#### TAU

Once patients are discharged from the hospital, they will be treated by the multidisciplinary team of the Intensive Early Intervention Programme for Incipient Psychosis (PAE-TPI) as part of their usual treatment, which consists of a multidisciplinary approach that includes pharmacological treatment and psychological support, as well as visits with social workers or nursing staff. An individual care plan is drawn up depending on the patient’s individual needs, which may include follow-up psychiatric visits to evaluate clinical status and, if necessary, readjust pharmacological treatment, and psychological visits to assess and detect risk situations and prevent relapses using a non-trauma focused CBT. The TAU psychological treatment will not under any circumstances be focused on PTSD or trauma symptoms.

### Dropouts and Follow-Up

Any patient who is admitted to hospital following a clinical relapse during the 5-month intervention period will be considered to be dropout and will be excluded from the trial. In the case of relapse during follow-up, patients will be removed from the study and relapse-related factors will be collected for subsequent analysis.

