Eye movement desensitization and reprocessing therapy (EMDR) is a psychotherapy based on standardized protocols, which integrates the use of bilateral stimulation (such as side-to-side eye movements) with elements of cognitive-behavioral, interpersonal and body-centered therapies (22). EMDR has been integrated into the World Health Organization guide as a first-line psychotherapy for the treatment of PTSD in adults, children and adolescents (for a review, see (23). Despite the high prevalence of comorbid PTSD in psychosis and the strong empirical evidence supporting the efficacy of this therapy, patients affected by psychosis have been commonly excluded from clinical trials related to trauma (24). However, this tendency has begun to change and early evidence shows that positive and affective symptoms in severe psychiatric disorders, as well as comorbid trauma-related symptoms, can be ameliorated by EMDR therapy (25, 26). A randomized controlled multicenter study has been conducted by (25), with a sample of 155 patients with chronic psychosis and comorbid PTSD. The results of this study demonstrated the efficacy of EMDR in the treatment of chronic PTSD symptoms in patients with a lifetime diagnosis of psychosis, with the therapeutic benefits maintained at the 6-month follow-up and a reduction in adverse events and revictimization. Several sub-analyses of the same study have demonstrated the efficacy of EMDR therapy also in patients with greater dissociative symptoms (27), with psychotic symptoms, depression and social functioning (25), and also a cost-effectiveness study in favor of EMDR therapy when compared to prolonged exposure (28).

Therefore, the main objective of the study is to evaluate the efficacy and safety of EMDR therapy in patients with an affective or non-affective FEP in the reduction of relapses, as well as the improvement of clinical symptoms, its possible positive impact on functioning and adherence to pharmacological treatment.

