### Study Aim

The main outcome of this project is to analyze whether EMDR therapy, as an adjuvant to TAU, is effective in reducing relapses in patients with an affective or non-affective FEP and a history of comorbid psychological trauma associated with first hospital admission and/or previous stressful life events. A range of scales, highlighted below, will be used to determine changes in psychiatric symptoms (see *Instruments and Measures*).

The secondary outcome includes whether EMDR therapy, as an adjuvant to TAU, is effective in reducing psychiatric symptoms and post-traumatic stress symptoms, in improving the overall functionality and quality of life associated with health, as well as adherence to pharmacological treatment. A range of clinical scales will be used the evaluate changes from baseline (see *Instruments and Measures*).

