### Hypotheses

1. Patients in the EMDR group will show fewer relapses compared to the control group after therapy (T1) and at the 12-month follow-up visit (T2).2. Patients in the EMDR group will show fewer psychiatric and trauma-related symptoms compared to the control group after therapy (T1) and at the 12-months follow-up visit (T2).3. Patients in the EMDR group will improve their functional capacity in comparison to the control group at evaluations after therapy (T1) and at the 12-months follow-up visit (T2).4. Patients in the EMDR group will show a better adherence to pharmacological treatment in relation to the control group after therapy (T1) and at the 12-month follow-up visit (T2).

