### Computation of Sample Size

The study aims to assess the relative efficacy of an EMDR intervention protocol for patients with FEP versus TAU mainly in terms of stabilization and clinical improvement, reduction of anxious, depressive, somatic and/or psychotic symptoms, among others. For this reason, the main variable used is the number of clinical relapses after the intervention, with a follow-up of up to 12 months. Using previous studies as a basis (33), the sample size has been calculated based on a survival analysis with the statistical package “powerSurvEpi” for R, (http://www.r-project.org/) using an alpha = 0.005 instead of 0.05 to allow correction for multiple comparisons. The number of patients required to detect a hazard ratio = 2 in a Cox regression with a statistical power of 80% and alpha = 0.005 is n = 36 per intervention group (two groups, total n = 72). According to Chambless and Hollon (29), a sample of this size should show clinically relevant differences. Assuming a loss percentage of approximately 10–15% of the patients in the study, it would be necessary to recruit approximately 80 patients, 40 for each branch of intervention.

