### Statistical Analysis

The distribution of socio-demographic, clinical (including psychological trauma), functionality, quality of life and treatment adherence characteristics among baseline groups will be analyzed using descriptive statistics. Continuous variables with a normal distribution will be analyzed with the Multivariate Variance Analysis. The change of the clinical variables of functionality and quality of life with respect to the baseline assessment at strategic points of the intervention will be analyzed by ANOVA with repeated measurements, including time factors, treatment conditions and their interaction. For those cases in which the premises of normality are not fulfilled, the Wilcoxon test will be used. The differences between groups, for the categorical and main clinical variables, will be analyzed by means of the Chi-square test. Those variables that are statistically significant can be used as covariates for a logistic or linear regression study of the factors associated to the magnitude of the effect and determine which variables are the best predictors of functioning. The effect size index (Hedges g or r de Pearson index) will be estimated in case of correlation indexes of each of the analyses performed. The statistical software used for the analyses will be the latest available version of the SPSS (v. 23).

For the main statistical analysis, we will conduct an intention-to-treat (ITT) analysis. We will impute lost to follow-up with the Last Observation Carried Forward (LOCF) method.

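### Patients admitted for relapse during therapy are excluded after randomisation, so the primary relapse comparison is selected by an outcome that treatment can shape, against the stated ITT analysis

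*Protocol article*

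**What the plan says.** All references are to the protocol article.

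- **Dropouts and Follow-Up, first sentence:** a patient admitted to hospital after a "relapse during the 5-month intervention period will be considered to be dropout and will be excluded from the trial".
- **Dropouts and Follow-Up, second sentence:** "In the case of relapse during follow-up, patients will be removed from the study and relapse-related factors will be collected for subsequent analysis". Data collection is therefore provided for follow-up relapses; nothing equivalent is stated for relapses during therapy.
- **Study Aim:** the main outcome is whether EMDR added to TAU "is effective in reducing relapses in patients with an affective or non-affective FEP", with no time window.
- **Computation of Sample Size:** "the main variable used is the number of clinical relapses after the intervention, with a follow-up of up to 12 months". The first objective in the abstract likewise speaks of relapses after intervention.
- **Hypotheses, no. 1:** "Patients in the EMDR group will show fewer relapses compared to the control group after therapy (T1) and at the 12-month follow-up visit (T2"). T1 is at 6 months and T2 at 12 months (Design and Study Setting).
- **Randomization Procedure:** allocation follows the baseline assessment, so it precedes therapy.
- **Statistical Analysis:** "For the main statistical analysis, we will conduct an intention-to-treat (ITT) analysis", with LOCF for loss to follow-up.
- **Introduction:** the main objective is to "evaluate the efficacy and safety of EMDR therapy" in this population.

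**The concern.** The rule removes randomised patients because of a post-randomisation event that is the trial's own outcome. If EMDR changes the risk of relapse while it is being given, in either direction, the patients left at month 5 are no longer comparable between arms. That is selection on an outcome of treatment, and it is incompatible with an ITT analysis. It also costs events in a small trial.

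Two further points follow. The sections disagree on when relapse counting starts: Study Aim sets no window, while Computation of Sample Size and the abstract start after the intervention. And although safety is part of the main objective, the article does not say that relapses during trauma processing are collected, whereas it does say so for later ones. If these patients leave the trial without outcome data, no later analysis can restore the comparison.

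**Working it through.** **The plan's own figures.** The article gives no relapse rate and no count of early relapses, so there is no figure of its own to reproduce on this point. Its only related figure is the sample size of 36 per arm. For a hazard ratio of 2, 80% power and two-sided alpha 0.005, the Schoenfeld formula needs 4(2.807 + 0.842)²/(ln 2)² ≈ 111 events, more than the 72 patients. The stated size therefore does not reproduce. That is a separate matter and nothing below depends on it.

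**1. Events and power lost.**

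From the article: 40 per arm, hazard ratio 2 (0.5 for EMDR against TAU), 5 months of therapy, alpha 0.005. Assumed: constant hazards, control 12-month risk p from 20% to 50%, and every relapse in months 0–5 leading to admission.

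- Control hazard: h = −ln(1 − p)/12.
- Relapses by month t: 40(1 − e^(−ht)) + 40(1 − e^(−ht/2)).
- Power: Φ(½√d · ln 2 − z), with z = 1.96 for alpha 0.05 and 2.807 for alpha 0.005.

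For p = 40%, h = 0.0426. Expected relapses by month 12 are 16.0 + 9.0 = 25.0. In months 0–5 they are 7.7 (TAU) + 4.0 (EMDR) = 11.7, which is 47%, leaving 13.3.

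| Control risk | All relapses | Months 0–5 | Kept | Lost, all admitted | Lost, half admitted | Power at 0.05 | Power at 0.005 |
|---|---|---|---|---|---|---|---|
| 20% | 12.2 | 5.4 | 6.9 | 44% | 22% | 23% → 15% | 6% → 3% |
| 30% | 18.5 | 8.4 | 10.1 | 45% | 23% | 32% → 20% | 9% → 4% |
| 40% | 25.0 | 11.7 | 13.3 | 47% | 23% | 41% → 24% | 14% → 6% |
| 50% | 31.7 | 15.4 | 16.3 | 49% | 24% | 50% → 29% | 20% → 8% |

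The power columns assume that all early relapses are admitted. If half are, power at 0.05 in the 40% row is 33%. If the 12 months run from the end of therapy (17 months in all, same risks at month 17), 31% to 35% of events are lost when all are admitted.

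**2. If excluded patients are kept through LOCF.** They would carry forward a relapse-free state. In the 40% row the true risk difference is 40.0% − 22.5% = 17.5 points. With early relapsers scored as relapse-free it is 8.4 points.

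**3. Direction of bias.** Suppose EMDR acts only during the 5 months, with TAU 12-month risk 40%. Let individual risk vary by a gamma frailty with mean 1 and variance v, so that S = (1 + vH)^(−1/v), where H is the cumulative baseline hazard.

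For v = 1 the monthly baseline hazard is (1/0.6 − 1)/12 = 0.0556. TAU survival is 0.783 at month 5 and 0.600 at month 12, so the risk after exclusion is 1 − 0.600/0.783 = 23.3%.

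- Hazard raised by 50% during therapy: EMDR survival is 0.706 and 0.554. The 12-month RR is 0.446/0.400 = 1.12. After exclusion it is 21.5%/23.3% = 0.92.
- Hazard halved during therapy: EMDR survival is 0.878 and 0.655. The 12-month RR is 0.345/0.400 = 0.86. After exclusion it is 25.5%/23.3% = 1.09.

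| Frailty variance | Early harm: 12-month RR → after exclusion | Early benefit: 12-month RR → after exclusion |
|---|---|---|
| 0 | 1.15 → 1.00 | 0.83 → 1.00 |
| 0.25 | 1.14 → 0.98 | 0.84 → 1.02 |
| 1 | 1.12 → 0.92 | 0.86 → 1.09 |

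So a therapy-period effect is hidden without frailty and changes sign with it.

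**The case against.** The best defence is that the main variable is worded as relapse after the intervention, so early relapses lie outside the counting window and are not deleted primary events. That wording is there, and the charge has to allow for it. It does not save the rule. A window that opens at month 5 still compares only those who reached it without a relapse admission, and it does not require randomised patients to leave the trial. Study Aim sets no such window.

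A second defence is that exclusion may mean only that visits stop, with the patient kept in the ITT set by imputation. The text allows this, but LOCF would then score a relapsed patient as not relapsed.

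Several stronger readings are tempting and are not supported:

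- **That the rule generally reverses the effect.** Reversal here needs both an effect confined to therapy and differences in underlying risk. Under a constant hazard ratio without frailty, the later hazard ratio is unbiased. Part of the gap between the two RRs is also definitional: one is a 12-month risk, the other a 7-month risk among those remaining.
- **That hypothesis 1 cannot be tested at T1.** This follows only if T1 counts from randomisation, and the wording is ambiguous.
- **That the safety signal is lost.** The article is silent on recording relapses during therapy. Adverse-event recording may stand in the full protocol, which is not shown.
- **That about half the events certainly go.** The rule covers only relapses with admission, and the share admitted is not given.

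**Conclusion.** The concern stands, and it needs correcting because it acts on the primary comparison. The exclusion contradicts the ITT statement and conditions the relapse comparison on an outcome that treatment can affect. This holds on either reading of the counting window, and LOCF does not repair it. The rule is stated outright, so it is not a detail left to an analysis plan.

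Its size depends on assumptions, because the article gives neither a relapse rate nor the share of relapses admitted. The loss is between about a fifth and a half of events in the scenarios above, with power at 0.05 at worst falling from 23%–50% to 15%–29%, and at the stated 0.005 from about 6%–20% to 3%–8%. Bias in the estimate, beyond lost power, requires an effect that differs between therapy and follow-up or patients who differ in risk. Neither is far-fetched: therapy ends at month 5, and the Limitations section concedes a heterogeneous sample.

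**What to change.** Reconcile Dropouts and Follow-Up with the abstract's objectives, Study Aim, Hypotheses, Computation of Sample Size and Statistical Analysis:

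- Delete the exclusion from the analysis, and state one counting window for the primary outcome: relapses from randomisation, in both arms.
- Keep all randomised patients in the ITT primary analysis and in outcome follow-up to T2. This includes patients who relapse during follow-up, whom the second sentence of that section now removes.
- Report relapses and admissions during the therapy period by arm.
- Relapse counted only after the intervention may stay as a labelled sensitivity analysis.

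The cost is a wording change plus continued T1 and T2 assessment of relapsed patients. In the 40% scenario that is about 12 early relapsers and about 25 relapsed patients in total out of 80, so the extra effort is modest but real. The change concerns trial follow-up and analysis only, not whether a patient continues therapy.

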## Materials and Equipment

### Instruments and Measures

Trauma-related symptoms will be evaluated using the instruments listed in **Table 2**:

Childhood Trauma Questionnaire (CTQ): The CTQ (36), Spanish validation (37), is a self-administered 28-item scale to measure abuse and neglect suffered in childhood on five subscales: emotional, physical or sexual abuse, and emotional or physical neglect, each subscale scored on a 5-point Likert scale. The score for each subscale classifies the severity of the abuse and neglect as: “none to minimal,” “low to moderate,” “moderate to severe” and “severe to extreme”.Global Assessment of Posttraumatic Stress Questionnaire (EGEP-5): The EGEP-5 (38) is a 55-item clinician-applied scale to determine PTSD diagnosis, based on the current DSM-V criteria. This scale consists of three sections: events, symptoms and functioning.The Holmes-Rahe Life Stress Inventory (39); Spanish validation (40) is used to determine which common stressful life events a patient has experienced in the last 12 months, with each life event scored according to a standardized measure of their impact (41) and a total score provided by summing all those applicable to the patient. Although individual characteristics and coping skills should be taken into account when interpreting scores, scores below 150 reflect low levels of stress, scores between 150 and 299 represent a 50% risk of a stress-related illness in the near future and scores above 300 represent an 80% risk (39).Impact of Event Scale - Revised (IES-R): The IES-R (42), Spanish validation (43), is a 22-item self-report measure used to determine the level of subjective distress the subject has experienced over the past week related to a specific stressful life event, with items corresponding directly to 14 of the 17 DSM-IV symptoms of PTSD. Each item is scored on a 5-point Likert scale from 0 to 4, yielding a total score ranging from 0 to 88, with subscale scores for Intrusion, Avoidance and Hyperarousal. Higher scores represent greater subjective distress.Dissociative Experiences Scale (DES): The DES (36), Spanish validation (44), is a 28-item self-report scale which measures the frequency with which an individual experiences a range of dissociative experiences, from normal to pathological. An overall mean score ranges from 0 to 100, and there are subscales for amnesia, dissociation and depersonalization. A total score of over 30 indicate high levels of dissociation.Dissociative Experiences Questionnaire (SDQ-20): The SDQ-20 (45), Spanish validation (46), is a 20-item self-report scale used to measure somatoform dissociation. Each item refers to a physical symptom and is scored from 1 to 5 on a 5-point Likert scale, ranging from “1 = this applies to me not at all” to “5 = this applies to me extremely”, and the patient is then asked if there is a known physical cause. Total scores can range from 20 to 100, with higher scores denoting higher levels of somatoform dissociation.

**Table 2 T2:** Measurements to evaluate trauma-related symptoms.

Clinical variable	Measurement interview/self-report	T0 Baseline	T1 Post-treatment 6 months	T2 Post-treatment 12 months
Childhood T.	CTQ	x		
PTSD	EGEP-5	x	x	x
Traumatic events	H-RLSI	x		
Trauma’s impact	IES-R	x	x	x
Dissociation	DES	x	x	x
Somatoform D.	SDQ-20	x	x	x

Childhood T, Childhood trauma; CTQ, Childhood Trauma Questionnaire; PTSD, post-traumatic stress disorder; EGEP-5, Global Assessment of Posttraumatic Stress Questionnaire; H-RLS,: The Holmes-Rahe Life Stress Inventory; IES-R, Impact Event Scale; DES, Scale of Dissociative Experiences; Somatoform D., Somatoform Dissociation; SDQ-20, Dissociative Experiences Questionnaire.

The diagnosis, clinical symptoms and level of functioning are to be assessed using the following instruments (see **Table 3**):

Suicide Module of Mini-International Neuropsychiatric Interview (MINI) (47): This is a short structured diagnostic interview, validated in Spain (48), which assesses the risk of suicide.A diagnosis of substance use disorder will be made according to DSM-5 criteria; the alcohol abuse and dependence and substance abuse and dependence modules of the MINI will also be used to determine diagnosis (48).Beck Depression Inventory (BDI-II): The BDI-II (49, 50), Spanish validation (51), is a 21-item clinician-administered scale designed for use with patients with a prior depression diagnosis, to quantitatively assess changes in the severity of depressive symptoms. Scores are summed and the total score indicates: 0–13 minimal depression; 14–19 mild depression; 20–28 moderate depression and 29–63 severe depression.Young Mania Rating Scale (YMRS): The YMRS (52), Spanish validation (53), is an 11-item clinician-applied scale which quantifies the severity of manic and hypomanic symptoms. Four items are given more weight to compensate for a lack of cooperation in acute patients and are graded on a 0 to 8 scale (irritability, speech, thought content and disruptive/aggressive behavior), while the remaining seven items are scored from 0 to 4. The scores are interpreted as follows: ≤12 indicates remission; 13–19 indicates minimal symptoms; 20–25 indicates mild mania, 26–37 indicates moderate mania and 38–60 indicates severe mania.Positive and Negative Symptom Scale (PANSS): The PANSS (54), Spanish validation (55), is an 30-item clinician-administered scale which measures positive, negative and general psychopathological symptoms on a scale of 1–7, based on the severity of the symptom. The semi-structured sci-PANSS interview (56), available in Spanish, will be used to facilitate the PANSS score.Global Assessment of Functioning Scale (GAF): The Spanish validation version of the GAF, which uses the acronym EEAG (57), is a brief measure of overall psychological disturbance, providing a global score ranging from 0 to 100. The lower the score, the poorer the functional status.

**Table 3 T3:** Measurements to evaluate diagnosis, clinical symptoms, and functionality.

Clinical variable	Measurement interview/self-report	T0 baseline	T1 Post-treatment 6 months	T2 Post-treatment 12 months
Diagnosis suicide	MINI	x		
Diagnosis S.	MINI	x		
Depression	BDI-II	x	x	x
Mania	YMRS	x	x	x
Psychotic S.	PANSS	x	x	x
Functionality	GAF	x	x	x

MINI, Mini-International Neuropsychiatric Interview; Diagnosis S, Diagnosis Substance; BDI-II, Beck Depression Inventory—II; YMRS, Young Mania Rating Scale; Psychotic S, Psychotic Symptoms; PANSS, Positive and Negative Symptom Scale; GAF, Global Assessment of Functioning Scale.

Quality of life associated with health, cognitive insight and adherence to treatment will be assessed using the following instruments (see **Table 4**):

Standardized Instrument for Evaluating Quality of Life Associated with Health developed by the EuroQol group (EQ-5D): EQ-5D is a standardized instrument developed by the EuroQol Group (58), available in a validated Spanish version (59), which provides a measure of health-related quality of life that can be used in a wide range of health conditions and treatments. It is comprised of five dimensions: mobility, self-care, usual activities, pain/discomfort and anxiety/depression. The total score ranges from 0 to 100, with lower scores indicating a poorer health-related quality of life.Beck Cognitive Insight Scale (BCIS): The BCIS (60), Spanish validated version (61), is a 15-item self-report scale designed to measure the level of awareness of having a mental disorder and the need for treatment. The scale comprises two sub-scales: self-reflectiveness (nine items) and self-certainty (six items), and a composite score of cognitive insight is given by subtracting self-certainty items from those pertaining to self-reflectiveness.Drug Attitude Inventory (DAI-10): The DAI-10 (62), Spanish validated version (63), is a 10-item scale for measuring attitude towards medication, with a total score obtained by summing the 10 items. In items 1, 3, 4, 7, and 10, if the answer is correct the score will be 2 and if it is false will be 1. In the rest of the items the correct ones score 1 and the false ones 2. The total score can oscillate between 10 and 20. There is no cut-off point but the higher the score, the more positive the perceived effect of the medication.

**Table 4 T4:** Quality of life, cognitive insight, and adherence to treatment.

Clinical variable	Measurement interview/self-report	T0 baseline	T1 Post-treatment 6 months	T2 Post-treatment 12 months
Quality life	EQ-5D	x	x	x
Insight	BCIS	x	x	x
Drug attitude	DAI-10	x	x	x

EQ-5D, Standardized Instrument for Evaluating Quality of Life Associated with Health developed by the EuroQol group; BCIS, Beck Cognitive Insight Scale; DAI-10, Drug Attitude Inventory.

